# Treatment regimen and dosage adjustment

After informed consent, each subject will be randomized to receive either oral aliskiren 300 mg/day or placebo for 16 weeks, followed by a washout period of 4 weeks, then crossed over to either placebo or aliskiren for another 16 weeks:

[figure not shown]

The appearance, packaging and labelling of the study medication and placebo would be identical. Individuals were randomised by a computer-generated list, which is used for packaging of the study item and then maintained by a third party that is not involved in the conduction of the study. Marked drug packs (35 capsules for each 4 week supply) will be designated for each patient. Both patients and investigators will be blinded. Results of biochemical tests will completed before the randomisation code is broken at the end of the study.

Based on the result of published study [Persson F, Rossing P, Schjoedt KJ, Juhl T, Tarnow L, Stehouwer CD, Schalkwijk C, Boomsma F, Frandsen E, Parving HH. Time course of the antiproteinuric and antihypertensive effects of direct renin inhibition in type 2 diabetes. Kidney Int 2008; 73: 1419-1425], a washout period of 4-weeks would be sufficient and baseline proteinuria level could be re-established.

During follow up visits, aliskiren will be dispensed by a dedicated research nurse; clinicians will be blinded from the treatment allocation.

*Concomitant therapy*

Prior to enrollment, all of the patients will be stable while receiving ACE inhibitor or ARB. Anti-hypertensive therapy will be titrated throughout the study period to maintain the blood pressure below 130 / 80 mmHg.

*Visit schedule*

Follow up visits will take place according to the following schedule:

- week –4 (screening)
- weeks 0, 2, 4, 8, 12, 16, 20, 22, 24, 28, 32, 36 and 40 (final visit)

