During every visit, the following parameters will be measured: body weight, blood pressure, pulse, adverse effects of treatment, complete blood picture, differential white cell count, renal function test, liver enzymes, serum calcium, phosphate, and early morning urine collection for protein-to-creatinine and albumin-to-creatinine ratio. Renal function is determined by the estimated glomerular filtration rate (GFR) according to a standardized formula validated in Chinese [19]. Serum fasting glucose and lipid profile will be measured at 0 and 16 weeks. Proteinuria will be measured by a turbidimetric technique with the Modular Analytics (Roche Diagnostics, Switzerland). Urinary creatinine (Jaffe's kinetic method) and albumin (immunoturbidimetry method) were also measured on the Hitachi 911 analyzer (Boerhringer Mannheim, Mannheim, Germany), using reagent kits supplied by the manufacturer.

During week 0, 4, 16, 20, 24 and 36, whole stream early morning urine will be collected for the study of gene expression in urinary sediment. The method of specimen handling has been described in our previous studies [16-18]. Based on these studies, the target genes to be quantified include nephrin, podocin, synaptopodin, ACE, ACE2, transforming growth factor beta-1 (TGF-1), connective tissue growth factor (CTGF), and hepatocyte growth factor (HGF). Urine supernatant will also be saved for the assay of TGF-1, CTGF and HGF by standard ELISA. At the same time points, we will also serum level of C-reactive protein (CRP), TGF-1, and angiotensin II will be measured by ELISA, as well as plasma renin activity (PRA) by conventional methods.

*End points*

Primary end point of the study is the change in the degree of proteinuria and albuminuria. Average levels proteinuria and albuminuria levels at –4 and 0 week will be taken as the baseline. Secondary end points include the rate of decline of estimated GFR (as determined by the least square method), and change in serum and urinary inflammatory markers.

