## Statistical analysis

Data will be expressed in mean  SD. The change in proteinuria, renal function and other inflammatory markers before and after treatment will be compared by paired Student’s t test or Wilcoxon’s matched-pairs signed-rank test as appropriate. Calculation will be performed by SPSS for Windows software version 11.5 (SPSS Inc, Chicago, IL).

JUSTIFICATION

The sample size is estimated by the Power Analysis and Sample Size for Windows software (PASS 2000, NCSS, Kaysville, Utah). We expect baseline proteinuria to be around 2.0 ± 0.75 g:g-Cr [20]. Given that in the recently published AVOID study [21] aliskiren led to a 20% additional proteinuria reduction on top of losartan 100 mg, a sample size of 57 would be needed to achieve 80% power, with a significance level (alpha) of 0.05, using a two-sided paired t-test.

TIMETABLE OF WORK

It takes 24 months to complete the study:

Enrollment of case September 2009 to November 2010

Follow up of case December 2010 to August 2011

Analysis and write up report September 2011 to December 2011

REFERENCE

1. D’Amico G. The commonest glomerulonephritis in the world: IgA nephropathy. Q J Med 1987; 245: 709-727.
3. Haas M. Histologic subclassification of IgA nephropathy: a clinico-pathologic study of 244 cases. Am J Kidney Dis 1997; 829-842.

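### Averaging is specified only for the week -4/0 baseline, which cancels from the aliskiren-minus-placebo contrast; averaging the last two visits of each period would be a cheap gain in precision

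*Protocol*

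**What the plan says.** The design is a randomised, placebo-controlled cross-over: 16 weeks on the first treatment, "followed by a washout period of 4 weeks, then crossed over to either placebo or aliskiren for another 16 weeks" (Protocol, Treatment regimen and dosage adjustment).

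Under End points: "Primary end point of the study is the change in the degree of proteinuria and albuminuria". The next sentence defines the starting value: "Average levels proteinuria and albuminuria levels at –4 and 0 week will be taken as the baseline". No on-treatment visit, single or averaged, is named for the other end of the change.

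The measurements listed for every visit include "early morning urine collection for protein-to-creatinine and albumin-to-creatinine ratio". By the Visit schedule, period 1 has on-treatment samples at weeks 2, 4, 8, 12 and 16. Period 2 has them at weeks 22, 24, 28, 32 and 36. Week 20 ends the washout and week 40 falls after treatment.

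Under Statistical analysis, changes "before and after treatment will be compared by paired Student’s t test or Wilcoxon’s matched-pairs signed-rank test as appropriate". For the sample size: "We expect baseline proteinuria to be around 2.0 ± 0.75 g:g-Cr", with a 20% additional reduction, 57 patients, 80% power and a two-sided paired t-test at 0.05.

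**The concern.** Averaging two samples at baseline suggests that a single spot urine ratio was thought noisy. The stated rule, however, covers only the term that the randomised comparison does not use. What remains in that comparison is the noise of the end-of-period values, and nothing is said about averaging there even though the samples will exist.

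If the analysis ends up using one spot value per period, the confidence interval for aliskiren against placebo will usually be wider than the collected data allow. A missed or outlying sample at week 16 or week 36 would then also remove or distort that patient's whole pair. At stake are precision and robustness, not bias.

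**Working it through.** **Inputs.** From the protocol: mean 2.0 and SD 0.75 g/g; effect 20% of 2.0 = 0.40 g/g; N = 57; two-sided alpha 0.05; paired t-test. Not given, so assumed over a range: the correlation rb between samples in different periods, and rw between late visits within one period.

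**1. The protocol's own figure.** With zero correlation between the paired values, the SD of the difference is 0.75 × √2 = 1.061. The exact noncentral-t calculation for 0.40 g/g then gives 58 patients, and power of 79.9% at 57. The stated 57 is therefore reproduced to within one patient, with rb = 0 implied. An SD of the difference of 0.75 (rb = 0.5) would give 30 patients.

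**2. Cancellation.** Let A and P be a patient's end-of-period values on aliskiren and placebo, and B the shared baseline. Then (A − B) − (P − B) = A − P, and B has gone, averaged or not.

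As an illustration, assume a sample-to-sample SD of 0.4 around a stable patient level:
- SD of A − P is 0.4 × √2 = 0.57 with a single, averaged or absent baseline.
- With two samples averaged at the end of each period it is 0.4 × √(½ + ½) = 0.40.

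For a before-after change the baseline does not cancel:
- single baseline, single end value: 0.4 × √2 = 0.57
- averaged baseline, single end value: 0.4 × √(1 + ½) = 0.49
- both ends averaged: 0.4 × √(½ + ½) = 0.40

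End-of-period averaging therefore helps under either analysis.

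**3. Size of the gain.** For a mean of m visits per period,

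Var(difference) = 2 × 0.75² × [(1 + (m − 1)rw)/m − rb].

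Going from m = 1 to m = 2 cuts the variance by the fraction (1 − rw) / [2(1 − rb)]. The equivalent N is 57 divided by (1 − cut).

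| rb | rw | variance cut | SE cut | equivalent N |
| --- | --- | --- | --- | --- |
| 0.4 | 0.5 | 42% | 24% | 98 |
| 0.4 | 0.6 | 33% | 18% | 86 |
| 0.5 | 0.6 | 40% | 23% | 95 |
| 0.5 | 0.7 | 30% | 16% | 81 |
| 0.6 | 0.75 | 31% | 17% | 83 |
| 0.7 | 0.8 | 33% | 18% | 86 |
| 0.7 | 0.9 | 17% | 9% | 68 |

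For rb 0.4-0.7 with rw 0.10-0.20 above rb, the range is 17-42% in variance, 9-24% in standard error and 68-98 in equivalent N. Outside that grid the gain can be smaller: at rb = 0.5, rw = 0.9 the variance cut is 10% (SE 5%), and it tends to zero as rw approaches 1. If rw is at least rb, the largest possible SE cut is 1 − √½ = 29%.

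**4. Interval width and power.** At rb = 0.6, rw = 0.75 the SD of the difference falls from 0.671 to 0.556. With t = 2.003 on 56 degrees of freedom, the 95% half-width falls from 2.003 × 0.671/√57 = 0.178 to 2.003 × 0.556/√57 = 0.148 g/g.

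Power at N = 57:
- 0.40 g/g, rb = 0: 80% rises to 90% (rw = 0.5) or 86% (rw = 0.7).
- 0.40 g/g, rb = 0.4: 95% with single visits. At rb = 0.6 it is already 99%.
- 0.20 g/g (half the planned effect), rb = 0.6, rw = 0.75: 60% rises to 76%.

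**The case against.** **Silence is not a decision.** A reader might infer that the plan uses one on-treatment value and discards the other samples. The protocol does not say that. It names no on-treatment value at all, and a paired test can take a mean as its after value just as it takes a mean as its before value. A statistical analysis plan not seen here may settle this. That objection stands, and the point is limited to what the protocol specifies. It remains fair to raise because the averaging rule was written into End points, for one side of the change only.

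**The baseline does not cancel in the test as worded.** Statistical analysis describes a before-after comparison, in which the averaged baseline helps. Nor would it cancel if week 20 served as the period 2 baseline. Both are true, so it would be wrong to call the baseline averaging useless. The cancellation applies to the aliskiren-placebo contrast with one shared baseline, which is the comparison that the randomised cross-over exists to make. Averaging the end values gains precision in the before-after test too.

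**Power is not short.** A reader might take the rise from 60% to 76% as evidence of an underpowered trial. It applies to half the planned effect. At 0.40 g/g the stated target is met even with rb = 0, to within rounding, and any positive correlation raises power further.

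**Late visits may not be exchangeable.** Antihypertensive therapy is titrated throughout, so weeks 12 and 16 are not perfect replicates, and the formula assumes equal variance and effect at both. This too stands, and is a reason to show the single-visit result alongside.

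**Conclusion.** The point holds as a cheap improvement in efficiency. The protocol specifies averaging only where the within-patient aliskiren-placebo contrast cannot use it, and gives the repeat on-treatment ratios no stated role in the primary end point. Nothing here is invalid or biased, and the documents do not support saying that samples are thrown away or that the trial is too small.

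The size rests on assumed correlations. For rb 0.4-0.7 and rw 0.10-0.20 above rb, with SD 0.75 g/g per sample, the standard error falls 9-24%. The documents alone do not fix the gain, which shrinks towards zero if late visits within a period are almost perfectly correlated. The benefit is chiefly a narrower interval, plus some protection against a missed or outlying sample. It matters for power at the planned effect only if the between-period correlation is near the zero implied by the sample size.

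**What to change.** In End points, define each patient's period outcome as the mean early-morning protein-to-creatinine ratio at weeks 12 and 16 for period 1 and at weeks 32 and 36 for period 2, on whichever scale is chosen for the primary analysis. Use the one available value if the other is missing. Do the same for the albumin-to-creatinine ratio. In Statistical analysis, base the aliskiren-placebo contrast on these two period means, and show the week 16/week 36 single-visit result as a sensitivity analysis. Keep the week -4/0 average to describe patients at entry.

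The cost is one sentence in End points and matching analysis wording, with no new visit, sample, assay or patient. The downside is that the end point becomes the effect over weeks 12-16 rather than at week 16, so it is slightly diluted if the effect is still growing after week 12.

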# Adverse events

Information about every adverse event will be collected and recorded. An adverse event is any undesirable symptom or medical condition occurring after starting the study medication, whether considered drug-related or not.

## Patient withdrawal

The patient will be withdrawn from the study for:

- death
- doubling of baseline serum creatinine level
- pregnancy
- any other intolerable adverse events
- significant non-compliance with the protocol
- the desire of the patient to withdraw from the study

All female patients will be advised on taking effective contraceptive measures during the study period.

## Statistical analysis

Data will be expressed in mean  SD. The change in proteinuria, renal function and other inflammatory markers before and after treatment will be compared by paired Student’s t test or Wilcoxon’s matched-pairs signed-rank test as appropriate. Calculation will be performed by SPSS for Windows software version 11.5 (SPSS Inc, Chicago, IL).

JUSTIFICATION

The sample size is estimated by the Power Analysis and Sample Size for Windows software (PASS 2000, NCSS, Kaysville, Utah). We expect baseline proteinuria to be around 2.0 ± 0.75 g:g-Cr [20]. Given that in the recently published AVOID study [21] aliskiren led to a 20% additional proteinuria reduction on top of losartan 100 mg, a sample size of 57 would be needed to achieve 80% power, with a significance level (alpha) of 0.05, using a two-sided paired t-test.

TIMETABLE OF WORK

It takes 24 months to complete the study:

Enrollment of case September 2009 to November 2010

Follow up of case December 2010 to August 2011

Analysis and write up report September 2011 to December 2011

REFERENCE

1. D’Amico G. The commonest glomerulonephritis in the world: IgA nephropathy. Q J Med 1987; 245: 709-727.
3. Haas M. Histologic subclassification of IgA nephropathy: a clinico-pathologic study of 244 cases. Am J Kidney Dis 1997; 829-842.

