This is an placebo-controlled cross-over study. We plan to recruit 57 patients with biopsy-proven IgA nephropathy.

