# Inclusion criteria

- aged 18-65 years
- requires anti-hypertensive therapy
- renal biopsy confirmed the diagnosis of IgA nephropathy
- proteinuria > 1 g/day (or proteinuria > 1 g/g-Cr) in 3 consecutive samples within 12 weeks despite ACE inhibitor or ARB treatment for at least 3 months
- estimated glomerular filtration rate > 30 ml/min/1.73m2
- willingness to give written consent and comply with the study protocol

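### The stated analysis is a paired before-and-after test and does not name the aliskiren-versus-placebo contrast that the randomised cross-over is built to estimate

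*Protocol*

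**What the plan says.** - **Design.** Protocol, Patients and Methods: "This is an placebo-controlled cross-over study". Under Treatment regimen and dosage adjustment, "each subject will be randomized to receive either oral aliskiren 300 mg/day or placebo for 16 weeks, followed by a washout period of 4 weeks", after which the patient receives the other treatment for 16 weeks. Capsules are identical, and patients and investigators are blinded.
- **End point.** Protocol, End points: "Primary end point of the study is the change in the degree of proteinuria and albuminuria", and "Average levels proteinuria and albuminuria levels at –4 and 0 week will be taken as the baseline". No comparator is named, and no baseline is set for the second period.
- **Analysis.** Protocol, Statistical analysis: "The change in proteinuria, renal function and other inflammatory markers before and after treatment will be compared by paired" Student's t test or the Wilcoxon signed-rank test. This is the only inferential analysis stated. The paragraph does not mention placebo, period or sequence.
- **Sample size.** Protocol, Justification: "We expect baseline proteinuria to be around 2.0 ± 0.75 g:g-Cr". The planned effect is a further 20% reduction over losartan, taken from a published trial. A two-sided paired t-test at 5% with 80% power gives 57 patients.

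**The concern.** The sentence fixes both a test and a contrast, and the contrast is before versus after. A randomised placebo period exists so that changes unrelated to the drug can be subtracted. A before-after change on aliskiren still contains them: titration of anti-hypertensives to a blood-pressure target throughout the study, any time trend, closer adherence within a trial, and some regression to the mean, since patients must exceed the proteinuria threshold "in 3 consecutive samples within 12 weeks despite ACE inhibitor or ARB treatment for at least 3 months".

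At stake is the primary conclusion. A significant fall on aliskiren could be reported as efficacy although placebo showed the same fall. Testing each treatment separately and finding one significant and the other not would not repair this, because that is not a test of their difference.

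This is more than detail deferred to a statistical analysis plan. The protocol itself states a contrast, and read as written it is not the randomised one.

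**Working it through.** **1. The plan's own figure.** Inputs from Justification: mean 2.0 and SD 0.75 g/g-Cr, a 20% effect, two-sided 5%, power 80%. The effect is 0.20 × 2.0 = 0.4 g/g. The SD of paired differences is not stated. With equal SDs and within-patient correlation ρ it is 0.75 × √(2(1 − ρ)).

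- ρ = 0: SD 1.061. The noncentral t gives N = 58, with power 79.9% at 57. The normal approximation gives 56.
- ρ = 0.5: SD 0.75. N = 30, with power 97.7% at 57.

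So 57 is reproduced to within one patient if paired values are taken as uncorrelated. The effect entered is an additional reduction, that is, a difference between treatments.

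**2. What the literal test does when aliskiren equals placebo.** Let proteinuria fall by m in both periods for reasons other than the drug. The before-after test on 57 patients has noncentrality m ÷ (SD/√57), and the critical t on 56 degrees of freedom is 2.003. For example, m = 0.2 and SD 0.75 give 0.2 ÷ (0.75/7.55) = 2.01, and rejection in 51% of trials.

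| Assumed common fall (g/g) | SD 1.06 (ρ = 0) | SD 0.75 (ρ = 0.5) | SD 0.58 (ρ = 0.7) |
| --- | --- | --- | --- |
| 0 | 5% | 5% | 5% |
| 0.05 | 6.4% | 7.8% | 9.8% |
| 0.1 | 10.8% | 16.7% | 24.8% |
| 0.2 | 28.8% | 50.8% | 72.4% |

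The falls and the correlations are assumptions. The 0.2 row is 10% of the planned mean.

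**3. How much fall can be supported.** Only regression to the mean has been put into figures. A log-normal simulation calibrated to about 2.0 ± 0.75, with three qualifying values above 1, gave 0.01 to 0.05 g/g for a within-patient coefficient of variation of 20 to 40%. That corresponds to rejection of about 5 to 10% over the SDs above. The figure depends on the model, and it would be larger if both baseline samples were also qualifying samples, which the protocol does not settle. For titration and trial effects the documents give no size.

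**4. Whether 57 still serves once the contrast is named.** For aliskiren minus placebo at the end of each period, the SD is again 0.75 × √(2(1 − ρ)):

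- N = 58, 41, 30 and 19 for ρ = 0, 0.3, 0.5 and 0.7, so 57 complete pairs give about 80% power or more throughout.
- Changes from the single week −4/0 baseline give the same contrast, because that baseline cancels within the patient.
- Contrasting changes from a separate baseline in each period has SD 0.75 × √(4(1 − ρ)). Power at 57 is then 51%, 66%, 80% and 95% for the same correlations.

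**The case against.** The strongest reply is that the sentence can be read charitably. What is compared may be each patient's change on aliskiren with the same patient's change on placebo, by a paired test. The blinded cross-over fits that reading. So does the sample size, which uses an additional reduction and a paired t-test. This stands as evidence of intent. It does not supply the missing words: the sentence names no second treatment, and no other section does so. It also leaves open which baseline applies in the second period, and step 4 of the working shows that this choice affects power.

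A reader might go further and infer that the placebo period will not be used, or that each treatment will be tested alone. The documents do not support that. They nowhere say that placebo data are set aside or that only aliskiren-period data are analysed.

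A reader might also take 29–72% as the error rate to expect. That is not supported either. It needs an assumed 0.2 g/g fall. Patients are to be stable on their ACE inhibitor or ARB before enrolment, and the baseline averages two visits. Both limit drift.

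**Conclusion.** The concern holds as an error in wording with a real consequence. The one stated analysis does not name aliskiren versus placebo. Taken literally, it is an uncontrolled test inside a placebo-controlled cross-over. Its 5% error for the drug question holds only if nothing but the drug changes proteinuria, and titration throughout the study makes that an unsafe premise.

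This conclusion does not depend on any particular drift. The size does: it runs from little above 5% to a large inflation, and the documents give no basis for choosing a point within that range. The intended analysis was probably the between-treatment one, so the defect lies in what is written rather than in the design or the data. It should be corrected before the randomisation code is broken, because it decides what the trial can conclude.

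**What to change.** Replace the sentence in Statistical analysis with:

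> The primary analysis is the within-patient difference, aliskiren minus placebo, in end-of-period urine protein-to-creatinine ratio and albumin-to-creatinine ratio (the value at week 16 or week 36, whichever ends the aliskiren period, minus the value ending the placebo period), estimated with adjustment for period (for example a mixed model with treatment, period and sequence that uses all randomised patients with available data) and reported with a 95% confidence interval. Before-after changes within a period are descriptive only.

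Use the same contrast for estimated GFR and the markers.

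Three features of this wording matter. The difference is defined by treatment, because week 16 against week 36 would be period 1 against period 2. Period is adjusted for, since time trend is one of the risks. The model accommodates patients who withdraw before the second period ends, for whom no paired difference exists. Both primary measures are kept, as in End points.

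The cost is slightly more analysis work. No new patients, visits or measurements are needed, because urine protein and albumin ratios are already collected at every visit.
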